### Exploratory endpoints/outcomes

The following exploratory/mechanistic outcomes will be measured:

Changes in the gut microbiome induced by capsulised FMT as measured by comparing between treatment groups change (relative to baseline) in the following.The proportion and relative abundance of bacterial taxa over time (days 10, 40, 100 and 190).The change in diversity of the microbiome over time (days 10, 40, 100 and 190) measured using Shannon and Simpson indices.Antibiotic resistance genes carriage over time (days 10, 40, 100 and 190)Changes in the gut metabolome induced by capsulised FMT (using nuclear magnetic resonance spectroscopy). Measured at days 10, 40, 100 and 190.Host immune response (T and B cells) as measured by comparing participants prior to and day 40, as well as donors who will act as controls.

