### Trial design

Randomised control participant-blinded, single-centre, feasibility trial with two parallel groups (FMT capsules and matched placebo). Eighty patients will be randomised 1:1 (40 will receive FMT capsules and 40 placebo) from eligible patients identified from Guy’s and St Thomas’ hospitals (figure 1 and box 1).

Box 1Participant inclusion/exclusion criteria**Inclusion criteria**To be eligible for enrolment, a participant must meet all the following criteria before undergoing any study-related procedures:Adult patients (age 18 years or older at time of consent).Current/previous patient at Guy’s and St Thomas’ NHS Foundation Trust.Ability to understand the purpose, potential benefits and risks of the study and capable of giving informed consent. The participant must be able to provide written informed consent.Documented gastrointestinal carriage of ESBL-E or CPE (stool sample) in the 21 days prior to consent.Symptomatic infection with the same target organism of interest in preceding 6 months (this needs to be microbiologically confirmed but is not restricted to any particular body site for example, could be urinary tract infection, intra-abdominal infection, blood stream infection).**Exclusion criteria**Pregnancy or planned pregnancy.Breastfeeding.Severe or life-threatening food allergy.Allergy or other contraindication to omeprazole, investigational medicinal product (IMP) or placebo ingredients.Treatment with systemic antibiotic on the day of and day prior to first IMP/placebo dosing to the end of the dosing period.Treatment with pre or probiotics in the 4 weeks prior to randomisation and for the duration of the study.Severe immunodeficiency.Systemic chemotherapy <30 days from baseline or planned chemotherapy within the upcoming 6 months.Known HIV infection with CD4 count <250 cells/uL.Known neutropenia with absolute neutrophils <1.0×10^9^.Prolonged treatment with corticosteroids (equivalent to prednisone >60 mg daily for >30 days) within 8 weeks of randomisation.Life expectancy <6 months.Swallowing disorder, oral-motor dyscoordination or likely inability/unwillingness to ingest study medication.Patients who have received another investigational drug or device within 4 months prior to randomisation.Any condition or circumstance, in the opinion of the investigator, that would compromise the safety of the patient or the quality of the study data.

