### Randomisation

The randomisation schedule will be generated using a validated online randomisation programme, hosted by King’s Clinical Trials Unit. The method of randomisation will be block randomisation with randomly varying block sizes. As this is a single-centre study, randomisation does not need to be stratified. Participants will be allocated treatment as close as possible to receiving it.

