### Data synthesis, analysis and presentation

A statistical analysis plan will be written by the trial statistician and signed off prior to database lock. The study will be reported in accordance with the Consolidated Standards of Reporting Trials extension for pilot and feasibility studies.

The proportion of patients who accept the offer of randomisation will be reported with 95% CIs computed by the exact binomial method. No statistical tests for significant differences between treatment groups will be performed. In addition to summary statistics of the secondary outcomes, all harms and withdrawals will be reported with 95% CIs. Patients will be analysed in the groups to which they are randomised in accordance with intent to treat principals.

The protocol has been designed to place minimal burden on patients and case report forms are only capturing essential data. It is inevitable that there may be some missing data, which will be reported by treatment group with reasons for missingness described, where possible. Since this is a feasibility study, we do not plan to impute missing data.

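### Arm differences in continuous microbiome measures are defined on change from baseline with no baseline adjustment stated, which can cost precision and carries chance baseline imbalance into the estimate (low priority)

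*Protocol article*

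**What the plan says.** The section Exploratory endpoints/outcomes opens with "The following exploratory/mechanistic outcomes will be measured". Its first item, microbiome change under FMT, is defined "as measured by comparing between treatment groups change (relative to baseline) in the following". Three measures follow: the proportion and relative abundance of bacterial taxa; diversity, given as "The change in diversity of the microbiome over time (days 10, 40, 100 and 190) measured using Shannon and Simpson indices"; and "Antibiotic resistance genes carriage over time (days 10, 40, 100 and 190"). No model is named and no baseline covariate is mentioned, here or elsewhere in the article. The metabolome item that comes next does not state a between-arm comparison of change.

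Other relevant statements:

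- Trial design: "Eighty patients will be randomised 1:1 (40 will receive FMT capsules and 40 placebo").
- Randomisation: "As this is a single-centre study, randomisation does not need to be stratified". Blocks of varying size are the only restriction.
- Data synthesis, analysis and presentation: "No statistical tests for significant differences between treatment groups will be performed". An SAP is to be signed off before database lock, and missing data will not be imputed.

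**The concern.** A raw change score subtracts the whole baseline value, so it gives baseline a weight of exactly 1. The best linear weight is the regression slope of follow-up on baseline. When that slope is below 1, the change score over-corrects. It adds baseline noise to the comparison, and the arm that happens to start lower tends to show the larger rise, whichever arm that is.

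A slope below 1 is plausible in this trial, though the article does not document it. Participants have had a symptomatic infection in the preceding six months, and most are expected to be inpatients. The antibiotic exclusion begins only the day before dosing: "Treatment with systemic antibiotic on the day of and day prior to first IMP/placebo dosing", continuing to the end of dosing. Some baseline stools may therefore be disturbed, and to differing degrees, with recovery over the following months in either arm. Unstratified randomisation does nothing to balance baseline diversity.

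What is at stake is how well the mechanistic estimates can be read. With no significance tests planned, readers will go straight to the estimates, so their precision and their sensitivity to the baseline draw matter. The article lists the mechanistic outcomes among the study's strengths.

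**Working it through.** **The plan's own figures.** The article gives no SD, correlation or precision figure for the microbiome comparison. Its only precision statement is for the consent rate: 40% with a 95% CI of 33 to 47 from about 200 approached. That reproduces (80/200, exact binomial: 33.2 to 47.1), but this point does not depend on it.

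**Inputs.**
- n = 40 per arm (Trial design). This is a best case; loss to follow-up raises both standard errors but leaves their ratio unchanged.
- Baseline SD sb, follow-up SD sf and their correlation rho are assumptions, so a range is shown.

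**General variances.** Per arm, in large samples:
- change score: sb² + sf² − 2·rho·sb·sf
- baseline-adjusted (ANCOVA): sf²·(1 − rho²)
- difference: (sb − rho·sf)², which is never negative. It is zero only when rho·sf/sb = 1, that is, when the slope on baseline is 1.

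**Equal SDs.** In SD units, with √(2/40) = 0.224:
- SE(change) = √(2(1 − rho)) × 0.224
- SE(adjusted) = √(1 − rho²) × 0.224
- ratio of SEs = √(2/(1 + rho))
- effective number out of 80 = 80·(1 + rho)/2

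| rho | SE change | SE adjusted | SE excess | 80 patients worth about |
|---|---|---|---|---|
| 0.3 | 0.265 | 0.213 | 24% | 52 |
| 0.5 | 0.224 | 0.194 | 15% | 60 |
| 0.7 | 0.173 | 0.160 | 8% | 68 |
| 0.9 | 0.100 | 0.097 | 3% | 76 |

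**Unequal SDs.** The variance ratio, change over adjusted, is 1 + (sb/sf − rho)²/(1 − rho²).
- sf = 2·sb, rho 0.5: 1 + 0/0.75 = 1.00, no loss.
- sf = 1.5·sb, rho 0.3: 1 + (0.667 − 0.3)²/0.91 = 1.15.
- If sf is smaller than sb, the loss exceeds the equal-SD figure.

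**Chance imbalance.** Let D be the baseline difference between arms. Given D, the change-score difference is shifted by (slope − 1)·D, which is −(1 − rho)·D with equal SDs. The adjusted difference is not shifted. For D of one standard error (0.224 SD), the shift is 0.16, 0.11, 0.07 or 0.02 SD at rho 0.3, 0.5, 0.7 or 0.9, opposite in sign to the imbalance. With a slope above 1 it would take the same sign.

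**Simulation check.** 10,000 trials of 40 + 40 with no true effect and equal SDs, at rho 0.3, 0.5 and 0.7:
- SD of the estimates, change against adjusted: 0.264 against 0.214, 0.224 against 0.195, 0.172 against 0.159.
- Slope of the change-score estimate on baseline imbalance: −0.70, −0.50, −0.30. For the adjusted estimate it was within 0.005 of 0.
- Mean of both estimators: within 0.006 of 0, so neither is biased over randomisations.
- ANCOVA on change and ANCOVA on the follow-up value gave the same treatment estimate to within 1e-14.

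**The case against.** The strongest reply is that the sentence defines an outcome, not a model. Change analysed with baseline as a covariate gives exactly the treatment estimate recommended here, so the wording is compatible with the fix, and the choice of covariates ordinarily belongs in an SAP that is not shown. This stands in part. A reader might infer that the trial has rejected baseline adjustment in favour of change scores; the article neither says so nor rules a covariate out. What remains is that the article does fix the contrast, and an analyst who follows it literally gets the less efficient estimate.

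Four other stronger readings also lack support:

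- **That every arm difference is affected.** The formulas suit continuous measures. They do not carry over directly to untransformed taxa proportions or to resistance-gene carriage, whose scale is not given. The secondary carriage endpoints are detected/not detected and use no change score.
- **That the method favours FMT.** The imbalance effect depends on the randomisation actually obtained. It can hide an effect as easily as mimic one.
- **That the metabolome has the same problem.** That item states no between-arm comparison of change.
- **That the placebo arm's main purpose is undermined.** The article justifies placebo chiefly by spontaneous loss of carriage, which bears on the carriage endpoints.

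It is also fair to say that the consequences are small. The outcomes are exploratory, no power is claimed and no between-group tests are planned. The low correlation is an assumption; at 0.7 to 0.9 with equal SDs the penalty is only 8% to 3%.

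**Conclusion.** The point holds in a limited form. Taken literally, the stated measure for continuous microbiome outcomes gives an estimate that in large samples is never more precise than the baseline-adjusted one, and that moves with chance baseline imbalance unless the slope on baseline is 1. The size rests on the assumed correlation and equal SDs; other SD ratios can shrink the loss to nothing or enlarge it. This is a missed and free gain in precision, not a contradiction or a bias. It leaves the consent-rate outcome, its progression bands and the carriage endpoints untouched, so the priority is low.

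**What to change.** Add one sentence under Exploratory endpoints/outcomes, or in the SAP. It should say that arm differences in the Shannon and Simpson indices, and in suitably transformed taxa abundances, will be estimated at each follow-up day (10, 40, 100 and 190) adjusted for the baseline value of the same measure. ANCOVA on the follow-up value or on change will do, since the treatment estimate is the same. Report each with a 95% CI and no significance test, in keeping with the planned analysis, and keep raw change from baseline as a descriptive summary.

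The cost is that sentence and one degree of freedom per model. The baseline value is already needed to compute change, so no further samples, visits or patients are required.

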### Patient population

Participants will be recruited from Guy’s and St Thomas’ NHS Foundation Trust, a 1200 bed academic centre in central London. It is anticipated that most patients will already be admitted to the hospital as part of standard of care treatment, thus, most activities will take place on the ward or clinical area that the patient is already located. Where this is not the case, participants will be invited to attend the infection clinical room on an outpatient basis.

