### Study intervention

FMT for this trial will be prepared in a lyophilised, encapsulated form in accordance with Good Manufacturing Practice principles and under manufacturing authorisation for an IMP from the Medicines and Healthcare Products Regulatory Agency. Our centre has recently provided FMT for a Clinical Trial of an Investigaional Medicinal Product (CTIMP) for cirrhosis and this follows similar processes.^20^ Healthy donor inclusion and exclusion criteria and screening and eligibility questionnaire are described in online supplementary table 3 and 4.

The product contains 0.9% sodium chloride and 5% trehalose (cryoprotectant) as excipients. A minimum of 80 g faeces from each donor will be used to manufacture one batch of five capsules. Following lyophilisation, the material will be encapsulated in five size 0 delayed release methylcellulose capsules (DRcaps, Capsugel, Livingston, UK). Placebo capsules will contain microcrystalline cellulose. The capsules for the FMT and placebo will be identical in appearance. The capsules are coloured Swedish orange, resulting in an opaque appearance through which the contents cannot be seen.

FMT donors are carefully screened healthy volunteers with a body mass index between 18 and 30. Donors undergo questionnaire screening for risk factors and testing for a range of infectious agents as previously described and in accordance with national guidelines (see appendix A for full details).^21^ FMT material is traceable from donor to recipient. Aliquots of donor stool will be kept for 30 years to allow for future testing if required.

At baseline, participants will have their medication history recorded, including over the counter preparations and supplements as well as pre/probiotics. Vital signs, height and weight and baseline blood biochemistry and haematology will be collected. Additionally, a serum sample will be stored to allow future testing in the event of a possible transmission event. If female and of childbearing age, a urinary pregnancy test will be performed. An EQ-5D questionnaire will also be administered.

Encapsulated FMT (IMP) and placebo will be dispensed by study staff to trial participants over 3 consecutive days (or over 5 days if over a weekend). Patients will be fasted for 4 hours and be pretreated with omeprazole on the morning on the FMT (40 mg on first dosing day and 20 mg on the 2 subsequent dosing days).

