### Evaluations during and after treatment

Follow-up events will be scheduled for all participants at 1 week, 1 month, 3 months and 6 months after end of therapy. If an outpatient, the visits at 1 week, 3 months and 6 months will be conducted by telephone, with the participant returning a stool sample by post. The follow-up at 1 month will be face to face and will include a blood sample for immune analyses. All visits will involve completion of an EQ-5D questionnaire (see figure 2 for additional details).

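### The exploratory immune endpoint is specified as a before/day-40 comparison with healthy donors as controls and does not name the randomised placebo arm, so as written it cannot isolate an effect of FMT

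*Protocol article*

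**What the plan says.** The immune outcome appears in the protocol article under Exploratory endpoints/outcomes. It is to be assessed "as measured by comparing participants prior to and day 40, as well as donors who will act as controls". Two comparisons are named, before against after and participants against donors, and the donors are called the controls.

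The microbiome outcome in the same list is assessed "as measured by comparing between treatment groups change (relative to baseline) in the following", which is the randomised contrast.

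Other sections bear on the point:

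- **Trial design:** 80 patients are randomised 1:1, 40 to FMT and 40 to placebo. Box 1 requires "Symptomatic infection with the same target organism of interest in preceding 6 months".
- **Patient population:** "It is anticipated that most patients will already be admitted to the hospital as part of standard of care treatment".
- **Study intervention:** "FMT donors are carefully screened healthy volunteers with a body mass index between 18 and 30".
- **Evaluations during and after treatment:** visits are planned for everyone randomised, at four times after dosing ends. On the blood sampling, this section adds that "The follow-up at 1 month will be face to face and will include a blood sample for immune analyses". Under Secondary feasibility endpoints the face-to-face visit is the day-40 visit.
- **Strengths and limitations:** the immune analyses, with the metagenomic and metabolomic ones, are put forward as a possible source of insight into how FMT works in patients who respond.

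No section of the article states a between-arm comparison of the immune measures.

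**The concern.** A before/after change in treated patients is the sum of several things: any effect of FMT, recovery from the qualifying infection or admission, other changes over the interval, and regression to the mean. Only the first is of mechanistic interest. The placebo arm is the group that shares all the others. Donors do not: they are selected for health, are not randomised, and have no recovery to undergo. Comparing participants with donors shows how far patients are from healthy people. It does not show what FMT did.

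The Discussion justifies the placebo by the need to control for spontaneous loss of carriage. The same reasoning applies to spontaneous change in immune measures, yet here the word for controls is given to the donors. What is at stake is the interpretation of one exploratory mechanistic outcome.

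**Working it through.** The article gives no figure for the immune endpoint (no variance, no expected change, no precision), so there is nothing of the plan's own to reproduce. The check has two parts.

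**1. What each comparison estimates**

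Let θ be the effect of FMT on the marker at day 40, and let δ be the change that would occur anyway (recovery, time, regression to the mean).

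| Comparison | Expected value | Isolates θ? |
|---|---|---|
| Before/day 40, FMT arm | θ + δ | Only if δ = 0 |
| Before/day 40, both arms pooled 1:1 | θ/2 + δ | No |
| Participants minus donors | Includes the pre-existing difference between patients and healthy volunteers | No |
| FMT change minus placebo change | (θ + δ) − δ = θ | Yes |

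The documents make δ = 0 hard to assume. Every participant has had a symptomatic infection within 6 months, and most are expected to be inpatients. The antibiotic exclusion in Box 1 runs only from the day before first dosing to the end of dosing, so antibiotic exposure may differ between the baseline and day-40 samples.

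**2. How much a drift could matter (assumed values)**

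Assumptions: θ = 0, 40 patients with both samples, and normally distributed change with standard deviation SDc. The probability that a before/after 95% CI excludes zero comes from the non-central t distribution with 39 degrees of freedom, critical value 2.023 and non-centrality (δ/SDc) × √40.

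| δ / SDc | Non-centrality | P(CI excludes 0) |
|---|---|---|
| 0.2 | 0.2 × 6.325 = 1.265 | 0.235 |
| 0.3 | 0.3 × 6.325 = 1.897 | 0.457 |
| 0.5 | 0.5 × 6.325 = 3.162 | 0.869 |

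Now express the drift in SDs of the marker itself. With pre/post correlation r, SDc = √(2(1 − r)) marker SDs, so at r = 0.5 the two scales coincide. Letting r run from 0.3 to 0.7:

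| Drift (marker SD) | P(CI excludes 0) |
|---|---|
| 0.2 | 18% to 36% |
| 0.3 | 35% to 67% |
| 0.5 | 74% to 98% |

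For the FMT-minus-placebo difference, δ cancels and the rate is the nominal 5% whatever the drift.

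**Precision of the randomised contrast (95% CI half-widths, marker SD)**

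- Change scores: t × SDc × √(2/n). With n = 40 and r = 0.5 this is 1.991 × 1 × √(2/40) = 0.45. The range over r is 0.34 to 0.53.
- Baseline-adjusted: 1.96 × √(2(1 − r²)/n). With n = 40 and r = 0.5 this is 1.96 × √(0.0375) = 0.38. The range is 0.31 to 0.42.
- If only 32 per arm give both samples (an assumed 20% loss), the ranges are 0.39 to 0.59 and 0.35 to 0.47.

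For comparison, the before/after half-width in 40 patients at r = 0.5 is 2.023 × 1/√40 = 0.32. The randomised contrast is therefore less precise, but it estimates θ.

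**The case against.** The strongest reply is that the text does not exclude the placebo arm. Participants means both arms, follow-up and the 1-month immune sample cover all of them, and the section on Data synthesis, analysis and presentation says patients are analysed as randomised. Adding donors does not remove the placebo group, and donors may be meant only as a healthy reference. This is one line on an exploratory outcome in a condensed article, with a statistical analysis plan still to come.

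Much of this stands. A reader might infer that the placebo arm has been replaced as comparator, or that recovery will be reported as an FMT effect. The documents support neither: a summary by arm remains possible, and how future authors will interpret the data is not stated. A reader might also put the donor gap down to age, but the article gives no ages for donors or patients.

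The illustrative percentages also have limits. No before/after CI in the FMT arm is planned for T and B cells. The Sample size section rules out tests within or between groups for the primary and secondary endpoints, and the analysis section rules out tests between groups. Qualifying infections may be up to 6 months old, so active recovery is an assumption for some participants. The Strengths and limitations statement is hedged and concerns responders, which a between-arm contrast alone would not settle.

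What does not fall away is the wording. The article specifies a comparison for this outcome, assigns the role of control to the donors, and differs from the microbiome item in the same list. That is a stated choice, not detail left for later. The bar on significance tests does not help either, because the before/after estimate is confounded whether or not it is tested.

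**Conclusion.** The point holds as a defect in how the comparison is specified. As written, the immune endpoint cannot separate an effect of FMT from recovery after infection, time effects or regression to the mean, and healthy donors do not supply the missing control.

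The size of the bias is unknown. The figures of about 46% to 87% rest on an assumed drift of 0.3 to 0.5 SD of the change, no FMT effect and 40 complete pairs. They show that moderate drift would be enough to mislead; they do not predict what this trial will find. The structural conclusion does not depend on them.

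The endpoint is exploratory. The consent-rate outcome, the progression criteria built on it and the carriage endpoints are untouched. The wording should be corrected before the analysis plan is signed off, but the point does not threaten the trial's main conclusion.

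**What to change.** Replace the comparison for the immune outcome with one sentence: change in T- and B-cell measures from baseline to day 40 (or the day-40 value adjusted for baseline) will be compared between FMT and placebo and reported as a difference with a 95% CI, without a significance test; donor values will be shown descriptively as a healthy reference. Before/after summaries can still be given, separately by arm.

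The cost is the sentence itself. The day-40 blood sample is already scheduled for all participants, and the pre-treatment sample is implied by the endpoint's own wording, so no extra patients or visits are needed. The price is a wider interval (half-width about 0.45 marker SD for change scores, or 0.38 with baseline adjustment, against 0.32 for before/after, at 40 per arm and r = 0.5). The change brings the item into line with the microbiome outcome and respects the bar on between-group tests.
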